**Other data**						
Days of delirium				x		
Days of invasive MV				x		
Days of ICU stay				x		
Days of hospital stay (including ICU stay)^b^					x	
Discharge destination^b^					x	
Days to return to work after ICU discharge (working age patients only)^c^					x	
Number of hospitals readmissions (excluding ICU readmissions)					x^d^	x^e^
Number of ICU readmissions					x^d^	x^e^
Psychopharmacological treatment^f^					x^d^	x^e^
Psychotherapy					x^d^	x^e^
Cognitive rehabilitation					x^d^	x^e^
Physical rehabilitation					x^d^	x^e^

*ICU* Intensive care unit, *MV* Mechanical ventilation

^a^Data automatically recorded by the RGS-ICU system in a secure cloud database, except for the number and reason for interruption or early termination of sessions, which will be recorded manually

^b^If the patient does not attend the 3-month follow-up visit, these data will be collected at the 12-month follow-up visit

^c^If the patient has not yet returned to work or does not attend the 3-month follow-up visit, this information will be collected at the 12-month follow-up visit

^d^The time elapsed between ICU discharge and the 3-month follow-up visit will be considered

^e^The time elapsed between the 3-month and 12-month follow-up visits will be considered. If the patient does not attend the 3-month follow-up visit, the time elapsed between ICU discharge and the 12-month follow-up visit will be considered

^f^Benzodiazepines, antidepressants, anticonvulsants/mood stabilizers and antipsychotics will be considered

#### Data management and confidentiality

Case Report Forms (CRFs) will be kept in locked file cabinets and all data will be entered in electronic CRFs (eCRFs) in a study-specific REDCap database protected by username and password. Patients will always be identified by a code, so that clinical data concerning them will never be linked to their personal data. In addition, personal and non-personal data will be stored in decoupled REDCap databases to ensure anonymity and confidentiality of the information collected. All records will be pseudo-anonymized and a master file linking the pseudo-anonymized data to patient identifications will be maintained within each center's network. Once this procedure has been carried out, the data will be integrated and stored in a relational database located in the servers of the University of the Balearic Islands-Research Institute of Health Science. From this moment on, aggregated and non-identifiable data will be used, maintaining a variable that is the origin of the data. The data will be securely stored in local servers protected by username and password access and will only be accessible by systems with secure virtual private network connection and secure credentials. All study staff will have access to the data for research purposes, with the obligation to maintain strict confidentiality. Data will be stored for at least 5 years after the end of the trial and then destroyed if no longer needed for research. Each partner will be responsible for data management in its respective center. Harmonization workshops will be organized to ensure that data are collected, assessed, and managed in a homogeneous manner. The staff trained to administer the intervention, collect and assess patient outcomes will be four investigators, two at the Parc Taulí University Hospital and two at the Son Llàtzer University Hospital.

#### Statistical methods

Results will be presented as mean (standard deviation) or frequency (%). Depending on whether the data have a normal distribution, parametric or nonparametric statistics will be used. In case of non-normal data, the median (range) will be reported. To compare results between the RGS-ICU and TAU groups over time, intersubject and intrasubject analyses will be performed, adjusting for multiple comparisons when necessary (e.g., Bonferroni correction). More specifically, intention-to-treat and per protocol analyses will be used. To address missing data, a last observation carried forward analysis together with a complete-case analysis will be performed. Where appropriate, analyses will be controlled for age, sex, delirium, invasive MV, type and dose of pharmacological treatment and/or cognitive reserve (CRQ). Effect sizes will be reported for all significant and non-significant data. Statistical significance will be set at *p* < 0.05. Analyses will be performed using the most recent version of the Statistical Package for the Social Sciences (IBM SPSS Statistics for Windows, Armonk, NY: IBM Corp).

To compare sociodemographic and clinical data between the RGS-ICU and TAU groups, an intersubject analysis will be performed. Intervention characteristics (e.g., session duration, protocols performed, etc.), intervention safety (i.e., number of sessions terminated early due to unsafe events on physiological parameters) and intervention tolerability (e.g., fatigue, extreme sleepiness, confusion) in patients assigned to the RGS-ICU group will be analyzed using descriptive statistics. To compare experienced comfort (PEECE) between the RGS-ICU and TAU groups, an intersubject analysis will be performed. To compare cognition (MoCA, WAIS-IV Forward Digit Span, WAIS-IV Backward Digit Span, RAVLT, TMT, SCWT, FAS, WAIS-IV Digit Symbol-Coding, SDMT and PDQ-5), mental health (GAD-7, PHQ-9 and TOP-8), functionality (WHODAS 2.0) and HRQoL (SF-12) between the RGS-ICU and TAU groups over time, intersubject and intrasubject analyses will be used.

Other analyses will include comparison of changes in the intensity of dyspnea, pain, worry and sadness (VAS) before and after each session in patients assigned to the RGS-ICU group. To this aim, an intrasubject analysis will be used.

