One such e-health solution is the Early Neurocognitive Rehabilitation in Intensive Care (ENRIC) platform. To the authors’ knowledge, this was the first non-immersive virtual reality (VR)-based cognitive intervention designed and developed specifically for patients with critical illness and the ICU environment (Clinicaltrials.gov Identifier: NCT02078206). In a first proof-of-concept (PoC) study (*n* = 20), Turon et al. [19] demonstrated the feasibility, safety, tolerability and potential efficacy of this intervention to stimulate the brain during ICU stay using a surrogate measure of cognitive function (i.e., heart rate variability, HRV). In a second randomized clinical pilot (*n* = 42, 21 experimental subjects and 21 control subjects), Navarra-Ventura et al. [13] demonstrated that cognitive stimulation with the ENRIC platform improved working memory performance shortly after ICU discharge and that this advantage was maintained in the long term, in line with results previously obtained using HRV. A trend toward reduced rates of anxiety and depression was also observed, although it did not reach statistical significance. However, this study was limited by an intervention that included only cognitive protocols but no specific relaxation content and by the high dropout rate related to the Covid-19 pandemic situation, with only 10 experimental subjects and 14 control subjects completing all post-ICU follow-up visits. Interestingly, in another PoC and pilot study (*n* = 20), Martí-Hereu et al. [20] demonstrated that watching videos of relaxing experiences using immersive VR goggles is feasible, tolerable and can help reduce anxiety during ICU stay in patients with critical illness.

Based on these and other experiences in stroke neurorehabilitation [21], a specific solution for patients with critical illness called Rehabilitation Gaming System for Intensive Care Units (RGS-ICU) was designed and developed that includes both cognitive stimulation protocols modeled after the ENRIC platform exercises and relaxing videos set in nature and fantasy landscapes to promote stress and anxiety reduction in patients with critical illness.

The following is the study protocol of a randomized clinical trial (RCT) using the RGS-ICU platform whose overall objective is to evaluate the efficacy and safety of cognitive stimulation and relaxation as an adjunct to standard ICU care (experimental condition) compared to standard ICU care alone (control condition).

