### Outcomes

The primary outcome is objective cognition 12 months after ICU discharge assessed with a global cognition index (z-score: mean = 0, standard deviation = 1) established on the basis of previous studies [6–8, 13, 14] and composed of validated neuropsychological measures of attention (Forward Digit Span subtest of the Wechsler Adult Intelligence Scale-IV, WAIS-IV), working memory (Backward Digit Span subtest of the WAIS-IV), learning/memory (Rey Auditory Verbal Learning Test, RAVLT), executive function (Trail Making Test, TMT; Stroop Color and Word Test, SCWT; FAS verbal phonemic fluency test) and processing speed (Digit Symbol-Coding subtest of the WAIS-IV; Symbol Digit Modalities Test, SDMT) [30–35].

The secondary outcome is the safety of the intervention assessed by considering the number of sessions terminated early due to unsafe events on physiological parameters [19].

Other outcomes are comfort experienced during ICU stay assessed at ICU discharge with the Patient Evaluation of Emotional Comfort Experienced questionnaire (PEECE) (range 0–48) [36], subjective cognition 12 months after ICU discharge assessed with the Perceived Deficits Questionaire-5 (PDQ-5) (range 0–20) [37, 38], anxiety 12 months after ICU discharge assessed with the Generalized Anxiety Disorder-7 questionnaire (GAD-7) (range 0–21) [39, 40], depression 12 months after ICU discharge assessed with the Patient Health Questionnaire-9 (PHQ-9) (range 0–27) [41, 42], PTSD 12 months after ICU discharge assessed with the Treatment-Outcome Post-Traumatic Stress Disorder Scale (TOP-8) (range 0–32) [43, 44], functionality 12 months after ICU discharge assessed with the World Health Organization Disability Assessment Schedule 2.0 (WHODAS 2.0) (range 0–100) [45], and HRQoL 12 months after ICU discharge assessed with the Short-Form Health Survey (SF-12) (range 0–100) [46, 47].

For all outcomes, except for intervention safety which is only evaluated in the RGS-ICU group, the difference between the RGS-ICU and TAU groups will be considered.

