### Participant timeline

The planned duration of the study is 24 months, starting in the summer of 2024. Patients will be enrolled consecutively during the first 12 months. The intervention will be administered daily during the ICU stay, as long as the patient's medical condition permits, and will end at ICU discharge or a maximum of 28 days after randomization, whichever occurs first. All participants will receive standard ICU care. Follow-up visits will be performed three and 12 months after ICU discharge (Fig. 5).

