### Sample size and power calculation

Sample size is based on the test of equality of two independent means for the primary outcome (objective cognition 12 months after ICU discharge) calculated using G-Power v3.1.9.7 software [48, 49]. Based on data from a randomized clinical pilot using the ENRIC platform [13], an eta squared effect size of 0.14 is anticipated. With a statistical power of 0.8 and a two-sided alpha level of 0.05, a minimum sample of 26 participants per group is needed to detect a Cohen's d effect size of 0.8 (total *n* = 52). Considering a dropout rate of 50% (15% during the ICU stay and 35% after ICU discharge), the minimum recruited sample needed for this RCT is 78 participants (*n* = 39 per group). Thus, at least 80 patients with critical illness (*n* = 40 per group) will be recruited, half of them in each participating hospital. However, since this RCT takes place in the ICU, it is to be expected that some dropouts will occur for reasons unrelated to the study itself (e.g., changes in health status that make continued participation inadvisable, mortality in the ICU, transfer to another ICU or withdrawal of consent previously given by an authorized representative). Thus, to maintain a sample size with sufficient power, these participants, estimated at 15%, will be replaced by new enrolments in a 1:1 ratio.

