#### Cognitive screening and experienced comfort data

On the day of discharge from the ICU, all participants will be administered the PEECE, a 12-item self-report questionnaire assessing subjective psychological well-being (Cronbach’s alpha = 0.74–0.88) [36]. The Montreal Cognitive Assessment (MoCA) test, a validated cognitive screening in survivors of critical illness, will also be administered [57, 58]. These data will only be collected if the patient is mentally competent.

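### LOCF beside complete-case analysis, with neither primary, mixes 3-month scores into the 12-month primary result

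*Protocol article*

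**What the plan says.** The protocol article fixes the endpoint and its timing under Outcomes: "The primary outcome is objective cognition 12 months after ICU discharge assessed with a global cognition index". The index is built from the attention, working memory, memory, executive and processing speed tests. Under Participant timeline, "Follow-up visits will be performed three and 12 months after ICU discharge", and the schedule after the ICU stay lists those tests at these two visits only. At ICU discharge the only cognitive measure is a screen: "The Montreal Cognitive Assessment (MoCA) test, a validated cognitive screening in survivors of critical illness, will also be administered". That screen is not among the components of the index.

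Statistical methods gives the whole handling of missing data in one sentence: "To address missing data, a last observation carried forward analysis together with a complete-case analysis will be performed". It does not say which of the two analyses decides the primary comparison. The same section promises both an intention-to-treat and a per-protocol analysis. Sample size and power calculation sets the expected loss: "Considering a dropout rate of 50% (15% during the ICU stay and 35% after ICU discharge". It counts death in the ICU among the in-ICU dropouts, who are to be replaced one for one. No rule is given for death after discharge.

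**The concern.** LOCF is a stated choice here, not a detail left open for a later analysis plan. With two visits it has one possible effect: a month-3 index is entered as if measured at month 12. This assumes that no patient lost in between improves or declines over nine months. The protocol sets objectives and hypotheses at both time points and plans comparisons over time, so it does not itself treat the two visits as interchangeable.

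The sole primary result is at stake. An early effect that fades could be reported in part as a 12-month effect, and a late effect could be diluted. Running complete-case analysis alongside does not settle this, because no rule says which result counts if they disagree. The complete-case comparison at month 12 also leaves out the month-3 scores of patients later lost, and it is valid only if loss is unrelated to outcome given the covariates used.

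**Working it through.** **The plan's own figure.** Sample size and power calculation states: "With a statistical power of 0.8 and a two-sided alpha level of 0.05, a minimum sample of 26 participants per group is needed". An eta squared of 0.14 converts to d = 2 × √(0.14/0.86) = 0.807, which the protocol rounds to 0.8. A two-sided two-sample t-test at d = 0.8 has power 0.8075 with 26 per group and 0.7915 with 25, so 26 reproduces.

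**How many values can be carried.** Take 40 per arm at ICU discharge, that is, after in-ICU dropouts have been replaced. A 35% loss leaves 40 × 0.65 = 26 observed at month 12 and 14 missing. If a share s of those 14 attended month 3, LOCF fills 14s values, and the month-3 weight is w = 14s / (26 + 14s).

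| Share s seen at month 3 | Carried per arm | Analysed per arm | w | Left unfilled per arm |
|---|---|---|---|---|
| 0 | 0 | 26 | 0 | 14 |
| 0.5 | 7 | 33 | 0.21 | 7 |
| 1 | 14 | 40 | 0.35 | 0 |

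**What LOCF then estimates.** With equal, random loss, the expected estimate is (1 − w) × d12 + w × d3, where d3 and d12 are the true effects at the two visits. Rejection rates come from simulation with 40 per arm, all 35% lost after month 3 (w = 0.35), equal SD at both visits and an assumed correlation of 0.7. Because each patient contributes one value and loss is random, the correlation does not affect these results.

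| d3 | d12 | Expected estimate | Rejection |
|---|---|---|---|
| 0.8 | 0 | 0.35 × 0.8 = 0.28 | about 22 to 23% (nominal 5%) |
| 0.4 | 0 | 0.35 × 0.4 = 0.14 | about 9% |
| 0 | 0.8 | 0.65 × 0.8 = 0.52 | about 60% |
| 0.4 | 0.8 | 0.52 + 0.14 = 0.66 | about 82% |
| 0.8 | 0.8 | 0.80 | about 95% |

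In the third row, complete-case analysis on 26 per arm would have power 0.81, so LOCF loses power although it analyses more values.

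Timing of loss matters. If 20% are lost before month 3 and 15% after, 6 of 32 analysed values per arm are carried. Then w = 0.1875, and the first row becomes 0.1875 × 0.8 = 0.15 SD with about 9% rejection.

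**Gain from a model that uses both visits.** Assume 32 per arm at month 3, 26 at month 12 and correlation ρ. The variance factor for the 12-month contrast is 1 − ρ² × (1 − 26/32).
- ρ = 0.6: 1 − 0.36 × 0.1875 = 0.9325; effective n = 26/0.9325 = 27.9 per arm.
- ρ = 0.8: 1 − 0.64 × 0.1875 = 0.88; effective n = 26/0.88 = 29.5 per arm.

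Power rises from 0.81 to about 0.83–0.86.

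**Unequal loss.** In the pilot, "with only 10 experimental subjects and 14 control subjects completing all post-ICU follow-up visits", out of 21 per arm: 11/21 (52%) against 7/21 (33%) did not complete. Suppose there is no effect, recovery of 0.3 to 0.5 SD between visits, and this imbalance falls entirely on carried values. The bias is then −(11/21 − 7/21) × recovery = −0.19 × 0.3 to −0.19 × 0.5, about −0.06 to −0.10 SD. It runs against the intervention, and rejection stays at about 5 to 7%.

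**The case against.** The strongest reply is that LOCF may do little harm here. The only evidence in the protocol on durability is the pilot's working-memory gain, which is reported to have persisted. If the effect is equal at both visits and loss is equal and random, LOCF leaves the mean difference unbiased. A drop from 0.8 SD to exactly zero is an extreme case, and a fading effect should show as disagreement between LOCF and complete-case results. The planned analyses over time also use the month-3 data. All of this stands as a limit on size. It does not justify the method: the protocol gives no ground for relying on a stable effect in the index, and no rule for resolving a disagreement.

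Four stronger readings are tempting, and the material does not support them.
- A reader might infer that LOCF turns the primary result into a 3-month effect. The month-3 weight is at most about 35% under the planned loss and can be zero.
- A reader might infer that the trial will score patients who have died. The protocol does not say so. In-ICU dropouts are replaced, anyone who dies before month 3 has no index to carry, and a life expectancy under 12 months is an exclusion. What remains is that the rule makes no exception for deaths between the two visits; their number cannot be derived.
- A reader might expect the LOCF standard error to be too small. With no effect at either visit, simulation gave a mean standard error of 0.224 against an empirical SD of 0.225, with 4.9% rejection. The excess rejection above comes from the shifted mean.
- A reader might take the pilot's unequal loss as a forecast. It is not significant (Fisher p = 0.35), it may include in-ICU loss, and the protocol links the high dropout to the pandemic. It is a caution only.

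**Conclusion.** The point holds. As written, up to 14 of 40 values per arm in the LOCF analysis can be month-3 scores labelled month 12, and no primary analysis is named to override it. At that upper limit the estimate moves 35% of the way from the 12-month effect to the 3-month effect. In the extreme cases this gives about 0.28 SD where the truth is zero, or about 0.52 SD where the truth is 0.8. The error shrinks as more of the loss falls before month 3, and it vanishes if the effect is stable and loss is equal and random. The visit-specific effects and the timing of loss are assumptions, because the protocol gives none of them.

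Two further defects follow from the text. Patients without a month-3 score cannot be filled, so LOCF does not deliver the promised intention-to-treat analysis. Death between the visits is not distinguished from other missing data.

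**What to change.** Make the primary analysis a mixed model for repeated measures on the global index at months 3 and 12, by randomised arm, with arm-by-visit terms and an unstructured covariance. Name the 12-month contrast as the result. SPSS fits this model. Drop LOCF and keep complete-case analysis as supportive. Add a multiple-imputation sensitivity analysis that includes a departure from missing at random. Patients with neither visit add no outcome data to the mixed model, so the imputation should cover them from data recorded in the ICU.

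State how deaths after discharge are handled. The mixed model does not solve this by itself: it implicitly extrapolates the month-3 scores of patients who die later, so it should not be described as a contrast among survivors. Report deaths by arm and add a sensitivity analysis that accounts for death.

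The cost is revised wording and a little more analysis work, with no new visits, patients or data. The gain in power is modest. The main benefit is a result that refers to month 12. The change should be made before the 12-month data are analysed.

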### Allocation and blinding

After initial consent, patients will be assigned to one of the two study arms using the Research Electronic Data Capture (REDCap) randomization module. A blinded study coordinator, who will not be involved in patient care, intervention, data collection or assessments, will manage this computer-generated procedure. Due to the characteristics of the intervention, neither other study staff nor patients will be blinded. Data collection and assessments will also not be blinded. However, an independent statistician will perform data analysis in a blinded fashion.

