**ICU data collection and assessments**					
Age at ICU admission		x			
Sex at ICU admission		x			
Education at ICU admission		x			
Reason for admission (principal diagnosis)		x			
Medical comorbidities at ICU admission (CCI)		x			
Severity of illness at ICU admission (SAPS 3, APACHE)		x			
Organ failure at ICU admission (SOFA)		x			
Mental status (GCS, RASS, CAM-ICU-7)		x	x	x	x
Ventilatory support (if any)		x	x	x	x
Weaning failure (if on MV)		x	x	x	x
Pharmacological treatment (type and dose in milligrams/day)		x	x	x	x
Dyspnea, pain, worry and sadness (VAS)^c^		x	x	x	x
Experienced comfort (PEECE)					x
Cognitive screening (MoCA)					x

*ICU* Intensive Care Unit, *RGS-ICU* Rehabilitation Gaming System for Intensive Care Units, *CCI* Charlson Comorbidity Index, *SAPS 3* Simplified Acute Physiology Score 3, *APACHE II* Acute Physiology and Chronic Health Evaluation II; SOFA, Sequential Organ Failure Assessment, *SpO2* Peripheral oxygen saturation, *RR* Respiratory rate, *HR* Heart rate, *GCS* Glasgow Coma Scale, *RASS* Richmond Agitation-Sedation Scale, *CAM-ICU-7* Confusion Assessment Method for the ICU-7, *MV* Mechanical ventilation, *VAS* Visual Analogue Scale, *PEECE* Patient Evaluation of Emotional Comfort Experienced, *MoCA* Montreal Cognitive Assessment

^a^Ability to lift and hold at least one upper extremity straight against gravity

^b^Continuous variables automatically monitored as part of standard ICU care to ensure the safety of the intervention

^c^Assessed once daily in patients assigned to the control (treatment as usual, TAU) group and before and after each session in patients assigned to the experimental (RGS-ICU) group, provided the patient is mentally competent

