#### Sociodemographic and clinical data

Age, sex, education, reason for admission (principal diagnosis), medical comorbidities (Charlson Comorbidity Index) [50], severity of illness (Simplified Acute Physiology Score 3 and Acute Physiology and Chronic Health Evaluation II) [51–54] and organ failure (Sequential Organ Failure Assessment, SOFA) [55] at ICU admission will be collected. Sequential data including mental status (GCS, RASS and CAM-ICU-7), mobility level (RGS-ICU group only), ventilatory support (none, non-invasive or invasive), weaning failure (if on MV) and pharmacological treatment (type and dose in milligrams/days) will be collected daily. Dyspnea, pain, worry and sadness will also be assessed once a day by visual analogue scales (VAS) with a range from 0 to 10 in patients assigned to the TAU group and before and after each intervention session in patients assigned to the RGS-ICU group, provided they are mentally competent.

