#### Cognition

Cognitive reserve will be assessed with the 8-item self-reported Cognitive Reserve Questionnaire (CRQ) (range 0–25) (Cronbach’s alpha = 0.80–0.96) [59, 60] and intelligence quotient (IQ) with the National Adult Reading Test, which provides a reliable estimate of premorbid IQ (*r* = 0.69–0.81) [61, 62]. CRQ and estimated premorbid IQ data will only be collected once at three or 12 months of follow-up.

Objective cognition will be assessed with the MoCA screening test [57, 58] and a comprehensive battery of validated neuropsychological tests including measures of attention (WAIS-IV Forward Digit Span subtest), working memory (WAIS-IV Backward Digit Span subtest), learning/memory (RAVLT), executive function (TMT, SCWT and FAS) and processing speed (WAIS-IV Digit Symbol-Coding subtest and SDMT). Raw data from neuropsychological tests will be standardized using population-based norms [30–35] and combined into a composite index of global cognition (z-score) established on the basis of previous studies [6–8, 13, 14].

Subjective cognition will be assessed with the 5-item self-reported PDQ-5 questionnaire (Cronbach’s alpha = 0.81–0.96) [37, 38].

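### Delirium, ventilation and drug dose are named as adjustment covariates, but as scheduled they are measured after randomisation and could carry part of the treatment effect

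*Protocol article*

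**What the plan says.** Under Statistical methods, the protocol states that "analyses will be controlled for age, sex, delirium, invasive MV, type and dose of pharmacological treatment and/or cognitive reserve (CRQ". The sentence opens with a condition (only where appropriate), and its last link is an and/or, so the covariate set is open. No analysis is singled out as the one to which the list applies.

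On timing:

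- Allocation and blinding: "After initial consent, patients will be assigned to one of the two study arms". Table 2 puts screening, consent and allocation on Day 0.
- Table 2 marks "Mental status (GCS, RASS, CAM-ICU-7" on Day 1 and every later column up to Day 28/ICU discharge, with no Day 0 entry. CAM-ICU-7 is the delirium measure.
- Sociodemographic and clinical data: "ventilatory support (none, non-invasive or invasive), weaning failure (if on MV) and pharmacological treatment (type and dose in milligrams/days) will be collected daily".
- Table 4 lists "Days of delirium" and days of invasive ventilation, both entered at Day 28/ICU discharge, which is when the intervention ends.
- Participant timeline: the intervention is given daily over the same ICU stay.

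The Background and rationale section names delirium, invasive ventilation and prolonged deep sedation as the main risk factors for the sequelae that the trial aims to reduce.

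**The concern.** A covariate may safely be adjusted for in a randomised comparison if allocation cannot have influenced it. Status on admission meets that test. Days of delirium, days of ventilation and milligrams of drug per day over the stay do not, because they accrue while one arm receives orientation, cognitive stimulation and relaxation.

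Two problems follow if the intervention shifts any of them:

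- The adjusted contrast leaves out the part of the benefit that runs through them. It is then no longer the effect of being allocated to RGS-ICU, which is what the intention-to-treat comparison and the sample size address.
- Illness severity drives both these variables and later cognition. Comparing patients with equal delirium or drug exposure across arms can therefore compare patients of unequal severity, with bias in either direction.

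Separately, a covariate list that applies where appropriate and joins its items with and/or allows different models to be tried and one to be picked. With about 52 planned completers and a multi-dimensional item such as drug type and dose, those models could differ noticeably.

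**Working it through.** **1. The plan's own figure.** Inputs from Sample size and power calculation: d = 0.8, two-sided alpha 0.05, power 0.8, two independent means. For n per arm, the noncentrality is d × √(n/2) on 2n − 2 degrees of freedom.

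- n = 26: 0.8 × √13 = 2.88, 50 df, power 0.807.
- n = 25: power 0.791.

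So 26 per arm is reproduced. It is a calculation for an unadjusted total effect.

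**2. Is a pre-randomisation value defined?**

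| Covariate | Recorded | Named summary |
|---|---|---|
| Delirium | CAM-ICU-7, Day 1 to Day 28/discharge | total days, at Day 28/discharge |
| Invasive ventilation | daily, Day 1 to Day 28/discharge | total days, at Day 28/discharge |
| Drug type and dose | daily, Day 1 to Day 28/discharge | none |

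Allocation is Day 0. For none of the three does the protocol name a baseline value as the covariate.

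**3. What adjustment would do if there is mediation.** The documents do not say how far the intervention alters these variables, so this is an illustration. Assumptions: one mediator M with within-arm variance 1; within-arm correlation of M with the outcome b = 0.5; total effect d = 0.8; mediated share m of 0, 25% or 50%.

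- Shift in the mediator: a = 0.8m/b.
- Effect left after adjustment: c = 0.8(1 − m).
- Approximate standard error with n = 26: √[(1 − b²) × (2/26) × (1 + a²/4)].
- Noncentrality c/SE on 49 df.

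| m | a | c | SE | c/SE | Power, formula | Power, simulation (4,000 runs) | Unadjusted, simulation |
|---|---|---|---|---|---|---|---|
| 0 | 0 | 0.80 | 0.240 | 3.33 | 0.90 | 0.90 | 0.82 |
| 25% | 0.4 | 0.60 | 0.245 | 2.45 | 0.67 | 0.65 | 0.79 |
| 50% | 0.8 | 0.40 | 0.259 | 1.55 | 0.33 | 0.32 | 0.81 |

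The adjusted estimates averaged 0.80, 0.60 and 0.40 in the simulation. The unadjusted comparison stays near 0.80 power throughout.

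**4. Break-even.** Under the same assumptions, solving the formula for adjusted power equal to 0.807 gives m of about 13%. Below that share, adjustment gains power; above it, adjustment loses power. At any share above zero, the adjusted estimate falls short of the total effect.

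This illustration has no unmeasured common cause of mediator and outcome, so it does not include the possible bias through severity.

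**The case against.** The best case for the plan has four parts.

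- **Adjustment is conditional.** A reader might infer that the primary estimate is bound to be adjusted for these variables. The text does not say so: the sentence is qualified, intention-to-treat is stated, and the sample size rests on an unadjusted comparison. This stands against any claim of certain bias. It does not excuse naming the variables, and the looseness is itself part of the problem.
- **A baseline version may be meant.** Data collection starts at ICU admission, the Day 1 column of Table 2 also holds admission items such as age and SOFA, and mental status is checked before each session. A value fixed before randomisation would answer the objection for delirium and ventilation status. But no such value is stated, and the reading does not fit drug dose in milligrams per day or the day totals in Table 4.
- **Mediation is not shown.** The protocol states no hypothesis that the intervention lowers delirium, ventilation or drug use. Being a risk factor shows prognosis, not mediation. Sessions also require patients to be near alert, so sedation before a first session cannot be caused by sessions. This stands: the loss is a possibility, and the mediated shares above are assumptions.
- **These variables are strong predictors.** If the intervention leaves them unchanged, adjusting raises power from about 0.80 to 0.90 in the illustration. This is a real benefit forgone.

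A reader might also infer that leaving hospital, education and premorbid IQ off the list is an error. The documents do not support that. A condensed article may leave such detail to a fuller document, age and cognitive reserve are listed, and scores are standardised to population norms. Estimated premorbid IQ is, moreover, obtained only at 3 or 12 months.

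**Conclusion.** The point holds in a limited form. The protocol names three covariates that, as scheduled, are measured after allocation and during treatment, and it defines no earlier version. Adjusting efficacy analyses for them can remove or distort part of the effect of allocation, and the open wording leaves the model to be chosen late. Blinding the statistician does not cure post-randomisation bias.

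The size is unknown. It ranges from no harm and some gain in power, if nothing is mediated, to a halved estimate and power of about 0.32, if half is mediated. Both ends rest on the assumed correlation of 0.5 and the 26 completers per arm that the plan targets. The documents do not show that the effect will be adjusted away, only that the stated rule permits it.

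**What to change.** State before the data are seen, for the primary and other efficacy models, a closed list of covariates fixed before randomisation: age, sex and, if wanted, delirium and ventilation status at or before randomisation. Hospital is a reasonable optional addition, since recruitment is planned with "half of them in each participating hospital". Replace the conditional wording with that list.

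Move delirium, ventilation and drug type and dose measured after randomisation to an exploratory mediation analysis, labelled as such. Use the Cognitive Reserve Questionnaire only in a sensitivity analysis. It aims at a premorbid trait, but it is collected at 3 or 12 months, after allocation, by unblinded staff.

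The cost is a sentence or two in the protocol or SAP. The one data point to secure is delirium and ventilation status at randomisation, which Table 2 does not now show on Day 0 but which the collection window from ICU admission would allow. The downside is losing the variance reduction that the later measurements would give if the intervention does not affect them.
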